The current literature suggests that older patients with mildly raised TSH concentrations may benefit from not being prescribed LT4 medication. The evidence is increasing and compelling to introduce age-specific TSH reference ranges for hypothyroidism regarding diagnostic thresholds and treatment targets to avoid patients being misclassified as having SCH and inappropriate treatment with thyroid hormones [13–15, 36, 37]. The distribution of TSH levels at the time of LT4 initiation has been described by Taylor et al., 2014 [33]. The median TSH when a patient is prescribed thyroid hormones has decreased from 8.7 mIU/L in 2001 to 7.9 mIU/L in 2009 in the UK, suggesting the likelihood a patient is prescribed LT4 treatment is increasing [33]. However, there has been a rising debate and emerging evidence suggesting that assessing borderline thyroid dysfunction may be more accurately characterised by fT4 levels rather than relying solely on TSH measurements [38, 39].

The literature is conflicting surrounding LT4 use and cardiovascular and bone health risk in the older population. A questionnaire answered by 408 individuals with SCH and taking LT4 found an increased risk of fractures in individuals over 50 years, particularly in the forearm [41]. It has also been found that the over-treatment of LT4 can increase the risk of cardiovascular morbidity, cardiovascular mortality and osteoporosis [42]. There is also conflicting evidence between the use of LT4 and mortality. The recent Baltimore Longitudinal Study of Ageing in 2021 found no association between all-cause mortality and LT4 use in over 65 year olds with normal TSH levels [43], while a much larger database study on 2,007,528 patients found that all-cause mortality was significantly higher in LT4-treated patients [44]. This suggests that LT4-based outcomes are dependent on both age and TSH levels.

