#### Inclusion criteria

Patients registered on the THIN database and aged over 50 on January 1st, 2006.Patients with a recording of TSH above 4.0 mIU/L between January 1st, 2006, and December 31st, 2021.Patients who are prescribed LT4 or receive no hormone replacement therapy. In the cohort study, patients in the treatment group will be prescribed LT4 before the end of the study period, December 31st, 2021. In the emulated target trial study, patients will initiate LT4 treatment and remain on it during a 5-year follow-up between January 1st, 2006, and December 31st, 2021. Patients in the emulated target trial study will be randomly assigned a strategy at baseline and be aware of their assignment.In the cohort study, patient follow-up ends at death, withdrawal from the database or December 31st, 2021, whichever occurs first.

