### Statistical analysis

The sample size calculation is based on the primary outcome of determining a difference in cardiovascular outcomes between patients receiving LT4 or not. The TRUST study of 737 patients aged 65 years and older found a cardiovascular outcome rate of 4.9% in the treatment group and 5.4% in the placebo group. Therefore, based on these outcome rates, for the cohort study, the minimum sample size required is 82,118 patients. Of this sample, 41,059 patients will be prescribed LT4 and 41,059 patients will not be prescribed LT4. A matching ratio of 1:4 (treatment: no treatment) will be used for the target trial emulation study. Therefore, the sample size required is 129,020 patients, with 25,804 patients prescribed LT4 and 103,216 patients not prescribed LT4. This sample size provides a power of 0.9 and alpha of 5%. In both studies, if missing data occurs, multiple imputation methods will be used if up to 40% of the data is missing [47]. Otherwise, pairwise deletion will be used.

In the target trial emulation study, the causal contrasts of interest will be intention-to-treat effect. Chi-square analysis will be used to compare the categorical characteristics of the participants in both studies, such that a p-value of less than 0.05 will be considered significant. Descriptive statistics will be presented. In both studies, the frequency of hypothyroidism diagnosis, smoking status, sex, ethnicity, and location will be given for each group. Survival analysis methods, including Cox proportional hazard models and Kaplan-Meier curves, will be fitted to compare the time to outcome between the groups. The hazard ratios with their 95% confidence intervals will be given.

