Confounding bias, immortal time bias, and information bias will be adjusted for both the cohort and target trial emulation studies [48]. In addition, selection bias and attrition bias will be adjusted for in the target trial emulation study. Confounding factors include sex, BMI, co-morbidities, and smoking status. The adjustment for confounding factors will be done using inverse probability weighting in the target trial emulation study [49]. In both studies, subgroup analysis will be done for each cardiovascular and bone health outcome and each age group (51–60, 61–70, 71–80, 81–90, 91 + years). A subgroup analysis including patients with a TSH level between 4 0.0 mIU/L and the upper limit of their age range in the TEARS study will be carried out. Another subgroup analysis of patients who have had a TSH level of 10 mIU/L or above or not will be conducted. Also, sensitivity analysis will be undertaken in both studies for different TSH thresholds, as the standard threshold can differ between laboratories. This study will perform a secondary analysis based on baseline fT4 levels, comparing patients with a low normal versus high normal levels (below and above median levels at baseline, respectively).

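### The secondary fT4 analysis is fixed as a sample-median split without naming the LT4 effect by fT4 as its target, and its lower half need not be low normal

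*Protocol article*

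**What the plan says.** The last sentence of the Statistical analysis section of the protocol article begins "This study will perform a secondary analysis based on baseline fT4 levels" and defines it as "comparing patients with a low normal versus high normal levels (below and above median levels at baseline, respectively". It names no outcome, model or treatment term. It follows a list of subgroup and sensitivity analyses by age, TSH level and TSH threshold.

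The reason for looking at fT4 is in the Background, which reports emerging evidence that "assessing borderline thyroid dysfunction may be more accurately characterised by fT4 levels rather than relying solely on TSH measurements". No reason is given for cutting at the median.

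The sample size is built on "determining a difference in cardiovascular outcomes between patients receiving LT4 or not", and all six objectives under Study aims compare patients prescribed LT4 with patients not prescribed it.

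On thyroid function, the inclusion criteria ask for "Patients with a recording of TSH above 4.0 mIU/L between January 1st, 2006, and December 31st, 2021". Neither the inclusion nor the exclusion list mentions fT4. The Background defines subclinical disease as raised TSH with fT4 in range, and overt disease as raised TSH with fT4 below range.

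**The concern.** Three features of the sentence weaken the analysis.

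- **Cut-point.** The median is a property of the sample. It would move with the TSH threshold in the planned sensitivity analyses and could differ between the cohort study and the emulated trial. It also puts patients just either side of the cut into opposite groups and treats each of them like the extremes of that group.
- **Target.** Read literally, the sentence compares two fT4 groups with each other. That describes fT4 as a prognostic factor. The Background rationale, that fT4 may better mark true dysfunction, points instead to whether the LT4 effect differs by fT4.
- **Label.** With no fT4 criterion at entry, a patient with raised TSH and fT4 below range meets the listed criteria and falls in the lower half. By the article's own definition that patient has overt disease, and the Background treats LT4 for overt disease as accepted. Such patients could distort the group of most interest.

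At stake is the precision and interpretation of one secondary analysis. The Discussion says the study may bear on LT4 prescribing, so a mislabelled fT4 group could mislead readers.

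**Working it through.** **1. The plan's own figures.** The article states no power or precision for the fT4 analysis. Its only calculation is for the primary outcome, from a cited trial that "found a cardiovascular outcome rate of 4.9% in the treatment group and 5.4% in the placebo group", with power 0.90 and alpha 5%. For two proportions with pooled variance, two-sided, no continuity correction and r untreated patients per treated patient:

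n(LT4) = [1.960·√((1+1/r)·p̄(1−p̄)) + 1.2816·√(p₁(1−p₁) + p₂(1−p₂)/r)]² / (p₁−p₂)², with p₁ = 0.049, p₂ = 0.054 and p̄ = (p₁+r·p₂)/(1+r).

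- r = 1: p̄ = 0.0515, n = 41,059.04 (stated: 41,059 per group, 82,118 in total).
- r = 4: p̄ = 0.0530, n = 25,804.46 (stated: 25,804 and 103,216, 129,020 in total).

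Both reproduce, and nothing below changes them.

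**2. Information kept by a median split.** If the true effect is linear in fT4, the efficiency of the split relative to a linear term is the squared correlation between X and the indicator that X exceeds its median.

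- Normal X: covariance = φ(0) = 0.3989 and indicator variance = 0.25, so efficiency = 0.3989²/0.25 = 2/π = 0.637. Loss 36.3%.
- Uniform X: covariance = 1/8 and variances 1/12 and 1/4, so efficiency = (1/64)/(1/48) = 0.75. Loss 25%.
- Normal truncated to a range (five truncations simulated): efficiency 0.648 to 0.691. Loss 31% to 35%.
- Lognormal, log-SD 0.1 to 0.3 (simulated): efficiency 0.631 to 0.590. Loss 37% to 41%.

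The article gives no fT4 distribution, so these shapes are assumptions. A much wider lognormal (log-SD 0.5) would lose 48%. Carrying the ratio over to an LT4-by-fT4 interaction also assumes a similar fT4 distribution in both treatment groups.

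**3. Dependence on the effect shape.** With normal X and a step effect in place of a linear one:

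| True effect | Median split keeps | Linear term keeps |
|---|---|---|
| Step at the median | 100% | 64% |
| Step at the 25th centile | 33% | 54% |

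**4. Power.** Take a linear effect that a 1-df linear test detects with 90% power. The mean of the test statistic is 1.960 + 1.2816 = 3.2415. After the split, power = Φ(3.2415·√0.6366 − 1.960) = 73.4%. From 80% power (mean 2.8016) it falls to 60.8%.

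For the same linear effect, a joint spline test with k df has the power of a non-central chi-square test with non-centrality 3.2415² = 10.507 (or 2.8016² = 7.849):

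| Test | From 90% | From 80% |
|---|---|---|
| 1-df linear | 90% | 80% |
| 2-df | 83.5% | 70.9% |
| 3-df | 78.4% | 64.5% |
| 4-df | 74.0% | 59.5% |
| Median split | 73.4% | 60.8% |

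The 36% loss is therefore measured against a 1-df linear test. Against a 4-df spline test the split loses almost nothing or nothing.

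**5. The label.** The criteria require TSH above 4.0 mIU/L and set no fT4 condition. The overt definition is raised TSH with fT4 below range. Any such patient not excluded on other grounds is eligible and, on any median that lies in range, is in the lower half. How many there are cannot be computed from the article.

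**The case against.** The sentence closes a run of analyses that all concern LT4 versus no LT4. It can be read as that contrast within each fT4 half, with the halves then compared. That reading is plausible, and a condensed article may leave the interaction model to a fuller plan. A reader might infer that the study does not ask whether the LT4 effect depends on fT4; the text does not support that. It supports only that the target is not stated. Nor does the article say that one median is taken over both treatment groups combined. That is the natural reading, but it is an inference.

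A reader might also take the one-third loss as established. It is conditional on the distribution and on a linear effect, and it vanishes for a step at the median. Nor is it the gain from a multi-df spline test.

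Finally, the words low normal and high normal, with the in-range definition of subclinical disease, may mean that only in-range fT4 is intended. If so, the label is right, but no restriction is stated. The missing fT4 limit is a study-wide eligibility matter, used here only for its effect on this label.

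What stands on any reading is that the median cut is written into the plan, depends on the sample and has no stated rationale.

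**Conclusion.** The point holds as a minor improvement to one secondary analysis. The article fixes a sample-dependent median split, does not state that the LT4 effect by fT4 is the target, and applies a low normal label that its listed criteria do not guarantee.

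Under a roughly normal fT4 and a linear log-hazard effect, the split keeps about 64% of the information of a linear term. That takes a test with 90% power to about 73%. Over the other assumed distributions the loss is about 25% to 41%, and it is nil for a step at the median. Nothing in the article points to a step there. The label problem needs no distributional assumption, but its size is unknown.

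**What to change.** Reword the sentence to:

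- state the target as the LT4 versus no-LT4 hazard ratio as a function of baseline fT4;
- restrict this analysis to patients whose baseline fT4 is within the reference range;
- keep fT4 continuous and test a 1-df linear LT4-by-fT4 interaction;
- use a restricted cubic spline to show the shape, not as the main test;
- keep the median split for display only.

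The cost is wording and one model, since fT4 values and dates are already among the variables captured. There are two downsides. A curve is slightly harder to present than two groups. An fT4 reference range must also be specified, because the variable list under Study setting names fT4 levels but no ranges. If ranges differ between laboratories, as the article says of the TSH threshold, the rule must say which range applies.

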## Discussion

The ACEL-UK study will add weight to the body of knowledge on this critical issue for ageing patients who are potentially experiencing significant harm from the possible over-prescription of thyroid hormones and will provide data to support or refute the concept of increased risk of cardiovascular and bone health risk in ageing patients. This study will look at LT4 treatment in ageing patients with mildly elevated TSH levels. The outcomes of this study may have implications for clinical practice and prescribing LT4 in the UK. Suggestions for future research after this study will include a randomised control trial with a large sample size to confirm the results of this study.

The main outputs will be reports (funder, local and national policymakers), academic publications, and national and international conference presentations. We will compile a summary report for publication in the Journal of Health Services Research to reach the NHS Commissioning Readership. We will disseminate our findings in popular GP press and peer-reviewed primary care and endocrine journals.

## Data Availability

The data that supports the finding of this study are available from THIN a wholly owned subsidiary of Cegedim SA who own the proprietary rights in THIN data. Restrictions apply to the availability of these data, which were used under license for the current study, and so are not publicly available. Data are however available from the authors upon reasonable request and with the permission of THIN. The datasets used during the feasibility study are available from the corresponding author on reasonable request.

## List of abbreviations

ACEL: UK Assessing the Cardiovascular Effects of Levothyroxine Use in an Ageing United Kingdom population
BMI: Body Mass Index
fT3: Free Triiodothyronine
fT4: Free Thyroxine
LT4: Levothyroxine
NHS: National Health Service
NIHR: National Institute for Health and Care Research
SCH: Subclinical Hypothyroidism
T3: Triiodothyronine
T4: Thyroxine
TEARS: Thyroid Epidemiology, Audit, and Research Study
THIN: The Health Improvement Network
TRUST: Thyroid Hormone Therapy for Older Adults with Subclinical Hypothyroidism
TSH: Thyroid Stimulating Hormone
UK: United Kingdom
US: United States
